## **5 Selection and Withdrawal of Subjects**

### **5.1 Subject inclusion criteria**

- Patients screened positive and diagnosed in a structured interview in different somatic specialties with a diagnosis of pain-predominant multisomatoform disorder and a Quality of Life score as measured with SF-36 of 1 standard deviation or more below population norm.
- Signed informed consent

### **5.2 Subject exclusion criteria**

- Age younger than 18 years
- Insufficient German language ability
- Insufficient cognitive abilities in the Mini Mental State (< 27)
- Severe and chronic somatic diseases (e.g. severe heart failure, encephalitis disseminata, dementia).
- Severe comorbid mental disorder causing major impairment of social functioning (e.g. schizophrenia, severe mood disorders, personality disorders, mental disorders due to substance abuse)

### **5.3 Subject withdrawal criteria (i.e. terminating intervention/ trial treatment) and procedures specification**

#### **a) When and how to withdraw subjects from the trial/ intervention**

A patient can be withdrawn from the trial for the following reasons:

- Revocation of informed consent
- Loss to follow-up

A patient can be withdrawn from trial intervention for the following reason:

- If a patient needs acute medical treatment for proven somatic disease for the symptoms on the basis of which he was initially included.

Withdrawal of subjects from the trial will be done after consulting with the coordinating investigator. It is his responsibility to inform the Trial Steering and Data Safety and Monitoring Committee of this event immediately.

#### **b) The type and timing of the data to be collected for withdrawn subjects**

##### **a) Whether and how subjects are to be replaced.**

Subjects will not be replaced during the trial. Drop out is taken into consideration in the sample size calculation.

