### 9.2. The number of subjects planned to be enrolled

Sample size calculation is motivated by the primary endpoint, based on the Physical Component Summary of SF-36 (PCS). We assessed the PCS for somatoform disorders in the general population with a mean value of 45,76 (SD=10.03) (Schmitz and Kruse, German National Health Interview and Examination Survey - Mental Health Supplement (GHS-MHS) 1998, public use file) and, clinically more realistically, with 37 (SD=12.5) in a sample of 186 patients in the University Hospital Heidelberg, treated in the outpatient departments for psychosomatics and orthopaedic chronic pain, comparable to the trial criteria (Henningesen et al. 2005).

In the trial an effect size of 0.5 is assumed, which is based on the following considerations: Clinically important change on the SF-36 PCS (ie what patients regard as important change) has been considered as follows: small change= 2.5; moderate = 4.5 and large = 6.5 (Wiebe et al 2002). In a previous trial of PIT in a functional somatic disorder (Creed et al. 2003), patients who received PIT improved by a mean of 5.5 points on the PCS compared to those receiving usual care, and this was associated with a reduction of median number of days of restricted activity per month from 5 to 0. Therefore, assuming an effect size of 0.50 on the basis of a standard deviation of 12.5 implies a clinically significant, large change of 6.25 in this measure of physical quality of life.

A sample size of 63 in each group will have 80% power to detect an effect size of 0.50 assuming a mean value of 37 in the control group and a known common standard deviation of 12.5 using a two group normal test with a 0.05 two-sided significance level.

This sample size calculation is based on the standard statistic

$$n = 2\sigma^2 / \theta^2 (z_{0.8} - z_{0.025})^2 \approx 63,$$

where  $\sigma^2 = 12.5^2$ ,  $\theta = 6.25$ ,  $z_{0.8} = 0.84$ ,  $z_{0.025} = -1.96$  and effect size is  $\theta/\sigma$ .

Several scenarios are considered for the number of patients per group. Table 1 shows a deterministic sensitivity analysis for different values of effect size. On the bases of the above requirements the sample size of  $n = 63$  per group was determined. Although, the sample size is very sensible to possible changes of effect size.

**Table 1.** Sample size estimation per group for different effect size and power ( $\alpha = 0.05$ , 2-sided).

| effect size | power 70% | power 80% | power 90% |

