|-------------|-----------|-----------|-----------|
| 0.6         | 34        | 43        | 58        |
| 0.55        | 40        | 52        | 70        |
| 0.50        | 49        | 63 | 84        |
| 0.45        | 61        | 78        | 103       |
| 0.40        | 77        | 98        | 131       |

In order to assess if the trial could be underpowered, a further probabilistic sensitivity analysis on the sample size and the power is carried out. This analysis puts uncertainty over the parameters  $\theta$  and  $\sigma^2$ . It is assumed that the prior mean of  $\theta$  is 6.25 with standard deviation 1, while for  $\sigma$  is assumed a prior mean of 12.5 and standard deviation of 1 (subject to the constraint of  $\sigma$  to be positive).

A Monte Carlo simulation method is applied to simulate values of  $\theta$  and  $\sigma^2$  from their prior distributions, substituting them into the sample-size formula and the resulted simulation values  $n_1^*, \dots, n_B^*$  recorded.

For a fixed  $n$ , the power is given by

$$power = \Phi(\sqrt{(n\theta/2\sigma^2)} + z_{0.025}).$$

If is decided to use 63 patients per group, values for the  $power$  can be simulated using the same methodology, resulting in simulated values  $power_1^* \dots power_B^*$ .

A total of  $B=10000$  simulated values  $n_b^*$  and  $power_b^*$  were carried out. Figure 1 gives the density estimation of these two quantities. They present a clear uncertainty for sample size and power values.

To achieve a fixed power of 80 % the median of the simulated sample size  $n^*$  is 88. For a fixed  $n=63$  the median of the simulated  $power^*$  values is 65%. These results indicates that the deterministic sample size calculation may give optimistic results and a larger sample size should be used to achieve a power of 80%.

Fixing  $n=88$  in the power formula and simulating again  $B=10000$  gives a median power of 79.6 %, which is more close to the trial power requirements. The recommended sample size for this trial is  $n=88$  per group.

**Figure 1.** *Left panel:* distribution for necessary sample size  $n$  to achieve 80% power. *Right panel:* power distribution with a fixed  $n = 63$  patients per group.

[figure not shown][figure not shown]

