### 9.4. Criteria for the termination of the trial

There are no formal statistical stopping rules defined for the trial. Premature study termination can be due to the following reasons:

- risk/ benefit ratio is changed
- DMSC recommends to stop the trial

Regular study termination will take place when the calculated numbers of patients in both arms have completed their follow-up.

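### Section 5.3 says dropout is built into the sample size, but section 9.2 has no dropout term; on the planning values 88 per group would tolerate up to 28% loss, which the protocol should state.

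*Protocol*

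**What the plan says.** Protocol section 5.3, on replacement of subjects, rules out replacement and adds: "Drop out is taken into consideration in the sample size calculation".

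Protocol section 9.2 derives the size in two steps.

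- The first is deterministic: "A sample size of 63 in each group will have 80% power to detect an effect size of 0.50", with SD 12.5 and difference 6.25. The formula contains only the SD, the difference and two normal quantiles.
- The second is a simulation that places uncertainty on the difference (mean 6.25, SD 1) and on the standard deviation (mean 12.5, SD 1). It reports a median n of 88 for 80% power and a median power of 65% at 63. It adds that fixing 88 "gives a median power of 79.6 %, which is more close to the trial power requirements". The recommended size is 88 per group, and the Protocol Summary gives 2 × 88.

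Protocol section 9.4 on the end of the study: "Regular study termination will take place when the calculated numbers of patients in both arms have completed their follow-up".

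Two other places bear on the point. Section 5.3 names revoked consent and loss to follow-up as reasons for leaving the trial. It also keeps patients who are withdrawn from the intervention in the same follow-up as completers and in the intention-to-treat analysis.

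**The concern.** The no-replacement rule rests on a dropout allowance that should be visible in section 9.2 and is not. Neither step there mentions attrition, and the move from 63 to 88 is attributed wholly to uncertainty about the difference and the standard deviation. The text available gives no attrition rate elsewhere.

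Participation lasts 16 months and the main endpoint is at 1-year follow-up, so some loss is to be expected. Because the protocol does not say whether 88 is the number randomised or the number analysed, a reader cannot tell whether there is a reserve. If 79.6% at 88 analysed is right, there is none. If the planning values behind the 63 are right, there is a large one. What is at stake is the stated basis for the trial's size and, secondarily, whether the end-of-study rule can be met.

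**Working it through.** **Inputs (Protocol 9.2).** Difference 6.25, SD 12.5, effect 0.50; 80% power, "using a two group normal test with a 0.05 two-sided significance level"; normal priors assumed for the simulation, independent, with the stated means and SDs (the protocol does not name the distributions). Loss of 10% to 30% is my assumption, since the protocol gives no rate.

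**1. The deterministic figure reproduces.** n = 2 × (12.5/6.25)² × (0.84 + 1.96)² = 2 × 4 × 7.84 = 62.7, so 63 per group. No dropout term enters.

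**2. The simulated figures do not reproduce.** Using the same n formula, and power = Φ(√(n/2) × difference/SD − 1.96):

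| Quantity | Protocol | From the stated priors |
|---|---|---|
| Median n for 80% power | 88 | 63 |
| Median power at 63 | 65% | 80% |
| Median power at 88 | 79.6% | 91% |

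This can be seen without simulation. Both n and power depend only on the ratio SD/difference. That ratio exceeds 2 exactly when SD − 2 × difference is positive. Under the priors this quantity is symmetric about 12.5 − 2 × 6.25 = 0. The median ratio is therefore 2, and the median n equals the deterministic 63. Putting the SD of 1 on the variance instead, or widening the prior on the difference to an SD of 2 to 4, also leaves the median at 63. Only a truncated prior on the standard deviation with an SD of about 12, not 1, comes close to the protocol (median n 87, power 66% and 80%). The power formula as it appears in the text has the difference unsquared. Taken literally it gives 20% at 63 and 26% at 88, so it is not what produced the protocol's figures either.

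**3. Effect implied by 79.6% at 88.** The normal quantile of 0.796 is 0.827, so the effect is (0.827 + 1.96)/√44 = 2.787/6.633 = 0.420. The protocol's 65% at 63 implies 0.418, so its simulated figures agree with each other, but on an effect of about 0.42 and not 0.50.

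**4. Power when 88 per group are randomised and a share L is lost.** Power = Φ(√(88(1 − L)/2) × effect − 1.96):

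| Loss L | Evaluable per group | Effect 0.42 (protocol's 79.6%) | Effect 0.50 (planning value) |
|---|---|---|---|
| 0% | 88 | 79.6% | 91% |
| 10% | 79.2 | 75% | 88% |
| 20% | 70.4 | 70% | 84% |
| 28.4% | 63 | 65% | 80% |
| 30% | 61.6 | 65% | 79% |

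The limit at effect 0.50 is 88 − 63 = 25 lost per group, and 25/88 = 28.4%.

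**5. Numbers to randomise, n/(1 − L), at 10%, 20% and 30% loss.** To keep 63 evaluable: 70, 79 and 90. To keep 88 evaluable: 98, 110 and 126. So 88 randomised covers the first target up to 28% loss and does not cover the second at all.

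**6. End-of-study rule.** If the calculated number is 88 per arm, 88 are randomised and nobody is replaced, one loss leaves at most 87 completers in that arm. Read literally, section 9.4 can then not be met.

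**The case against.** The best defence is that 88 works as an allowance whatever its origin: it is 25 above the 63 needed at effect 0.50. That stands for the power, but it does not rescue the sentence in 5.3. Section 9.2 gives another reason for the 25 and names no loss rate, so reading 88 as 63 inflated for dropout is a reader's inference. A separate analysis plan would not cure this either, because the protocol makes the statement and presents the calculation itself.

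A reader might go further and infer that the stated power holds only if nobody is lost, or that the trial is too small. The documents do not support that. It is true only of the 79.6%, which does not follow from the stated priors and is already just below 80% with no loss. The 80% at effect 0.50 survives the loss of 25 of 88 per group.

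Two further points limit the concern, and both stand. Patients who only stop the intervention remain in follow-up and in the analysis, so only revoked consent and loss to follow-up reduce the number analysed. And section 9.4 can be read as the planned cohort reaching the end of its follow-up; the Protocol Summary also sets calendar limits (follow-up in months 20 to 31, 36 months in all), so an endless trial is not a realistic consequence. The rule remains loosely worded, but it is a secondary matter.

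One caution runs the other way. The same surplus cannot fully serve two purposes. By the protocol's own Table 1, 80% power needs 78 per group at effect 0.45, which would leave room for only 10 of 88 (11%) to be lost, and 98 at effect 0.40, which is more than 88 before any loss.

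**Conclusion.** The point holds as a contradiction between sections 5.3 and 9.2: the protocol claims a dropout allowance that its calculation does not contain. Its size depends on which of the protocol's figures is used. On the 79.6% taken at face value there is no reserve, and 10% to 30% loss would bring power to about 75% to 65%. On the planning values (effect 0.50, SD 12.5, two-sided 0.05, normal approximation) there is an undeclared reserve of 25 per group, and power stays at or above 80% up to 28% loss. The second basis is the one that reproduces. The conclusion assumes that a lost patient contributes nothing to the 1-year comparison, and it sets aside the centre and setting effects of section 9.1, which section 9.2 also ignores. It raises no question of bias or type I error. What needs correcting is the stated justification of the trial's size.

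**What to change.** - **Section 9.2.** Rerun the simulation, and correct its results, its power formula or its stated priors so that they agree. Say that 88 per group is the number randomised, that 63 evaluable per group gives 80% power at effect 0.50, and that 88 therefore tolerates up to 28% loss at 1 year on the planning values. State the expected loss from revoked consent and loss to follow-up. If part of the surplus is still meant to cover uncertainty in the effect or the standard deviation, say how much is left for loss.
- **Section 5.3.** Point the dropout sentence to that figure, or delete it.
- **Section 9.4 (secondary).** Let the study end when every randomised patient has reached the 1-year assessment or has left follow-up.

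The cost is one short rerun and wording in three sections. No additional patients are needed on the planning values, provided that the expected loss does not exceed 28%.

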##### **b) The follow-up for subjects withdrawn from interventional treatment/trial treatment**

- The follow-up for patients who are withdrawn from the interventional treatment will be identical to the follow-up of completers. These patients will be included in the intention-to-treat analysis.

## **6 Treatment of Subjects**

### **6.1. The treatment(s) to be administered, including the dose(s), and the treatment period(s), including the follow-up period(s) for subjects for each intervention/trial treatment group/arm of the trial.**

#### **Experimental Intervention**

Manualized phase –defined 12 session intervention based on the principles of psychodynamic-interpersonal psychotherapy (Rudolf and Henningsen 2003, Margison 2002) applied to the purposes of patients with organically unexplained bodily symptoms (Guthrie et al. 1999).

#### **Control Intervention**

Enhanced medical care for the respective symptom leading to current health care utilisation. In order to increase motivation of patients in the control intervention, in addition to “treatment as usual” they will take part in three monthly manual-defined case management counselling interviews aimed at increasing self care skills and shared decision making in illness behaviour.

The treatment period will be 12 weeks/ 3 months in both limbs of the trial, the final assessment will take place after three months and follow-up at one year.

**6.2. Medication(s)/treatment(s) permitted (including rescue medication) and not permitted before and /or during the trial.**

Medication as prescribed by the General Practitioner and/ or the treating somatic physician(s) is permitted during the trial. Medication type and dosage will be monitored closely.

**6.3 Procedures for monitoring subject compliance**

Special ascertainment of non-compliance is not necessary in the planned trial as patient's absence from therapy sessions is obvious and will be documented.

**6.3. Procedures for monitoring treatment adherence by the therapist**

All therapy sessions will be audio taped. Integrity of therapy will be monitored through regular supervision and independent rating of a random sample of audiotapes (2 sessions/ therapy) using the Sheffield Psychotherapy Rating Scale (Startup and Shapiro 1993). Therapists will fill out the adherence scale after every second session in order to prevent drift.

Furthermore only therapists experienced in the use of psychodynamic-interpersonal psychotherapy will take part in the study. All therapists will be trained together in the application of the treatment manual in a central workshop before starting the treatment period; booster training sessions will aim at maintaining and further increasing therapist adherence.

**7. Assessment of Efficacy**

**7.1. Specification of the efficacy parameters and justification for their clinical relevance**

Efficacy of the intervention will be determined through the primary and secondary endpoints of the trial as described in 4.1.

Treatment effects in patients with multisomatoform disorder, if present, regularly show up primarily in a lesser degree of impairment by the symptoms rather than in a disappearance of the symptoms – in keeping with the notion that somatoform disorders are “disability syndromes”. Therefore it is justified to use a health related quality of life measure as primary endpoint. The secondary endpoints all assess important aspects either of psychopathology or of potential mediators of change. Information about validation of the measures is given above.

**7.2. Methods and timing for assessing, recording, and analysing of efficacy parameters**

Efficacy parameters will be assessed before and after the treatment period and after one year. Most efficacy parameters are self-report data. In addition, there will be an assessment of psychophysiological measurements at three month.

**8. Assessment of Safety**

**8.1. Specification of safety parameters.**

All complications and unanticipated adverse events will be reviewed by the coordinating investigator. The coordinating investigator is responsible for identifying issues that warrant immediate action and the evaluation of trends of consequence.

For the purposes of this study we will define adverse and serious adverse events according to the ICH-GCP guidelines (guidelines for Good Clinical Practice; ICH-Harmonised Tripartite Guideline; EMEA Status as of June 1996) as follows:

Adverse Event (AE): Any untoward medical occurrence in a patient or clinical investigation subject which does not necessarily have a causal relationship with this treatment. An adverse event (AE) can therefore be any unfavourable and unintended sign (including an

abnormal laboratory finding), symptom, or disease temporarily associated with the treatment investigated in the study, whether or not related to the treatment product.

In PISO, AEs are likely to occur with medium to high frequency, as the population studied is defined by frequent and frequently changing somatic symptom complaints. It is up to the investigator at the respective trial site to decide whether complaints of the patients are to be seen as anticipated in this sense or whether they are judged as being unanticipated and hence necessitate immediate information of the coordinating investigator.

Serious adverse event (SAE): Any untoward medical occurrence that:

- results in death,
- is life-threatening,
- requires inpatient hospitalisation or prolongation of existing hospitalisation,
- results in persistent or significant disability/incapacity
- congenital anomaly or birth defect.

In PISO, increased depressivity and/ or suicidality is considered as SAE and should be reported in the same way.

#### **8.2. Methods and timing for assessing, recording and analysing safety parameters**

Assessment of bodily and other complaints as well as of depressivity and suicidality is an integral part of the 12 treatment sessions in the experimental intervention and of the 3 case management sessions in the control condition within PISO.

Each treatment session will be audiotaped, in addition, written notes of the relevant aspects of the session will be kept by the therapist.

All safety parameters will also be recorded at final assessment at 3 months and follow-up at 1 year.

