#### **Risks**

As it is based on common therapeutic strategies in patients with medically unexplained symptoms, the intervention in PISO is not experimental. Psychotherapeutic interventions like this have repeatedly been shown to be relatively safe, but all have potential side effects. In particular, there is a risk that during the intervention patients may transiently become more depressive and/ or suicidal as a sign of altered emotional processing of life stresses. Close monitoring of this risk by the therapist is assured through the PIT manual and is helped by the fact that the intervention is taking place not in group, but in single patient format. Appropriate action (e.g. antidepressive medication, psychiatric in-patient referral) is defined in a manual for clinical care that will be adapted to the local situation of each centre.

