#### Secondary endpoints

- **IPQ, Brief Form**

The brief form of the „Illness Perception Questionnaire“ (BIPQ, Broadbent et al. in submission) provides a quantitative measure of the components of illness representations (identity, consequences, timeline, personal control, treatment control, emotional representations, illness coherence, psychological attributions, risk factor attributions) that has been shown in treatment trials to be sensitive to change. The German version was developed and validated by Gaab (unpublished manuscript) (t 0, t 1, t 2).

- **PHQ-D**

The „Patient Health Questionnaire“, German version (PHQ-D) is a brief self-report measure for anxiety, depression and other mental disorders. Criterion validity was established with respect to diagnostic gold standards and the PHQ has proven to be a responsive and reliable measure of depression treatment outcome (Löwe et al. 2004) (t 0, t 1, t 2).

- **SOMS-7**

Seven-day version of the „Screening for Somatoform Symptoms“. A 53-item instrument for the evaluation of treatment effects in somatoform disorders, covering all somatic symptoms occurring in somatization disorder, according to DSM-IV and ICD-10 (Rief and Hiller 2003)(t 0, t 1, t 2).

- **Whiteley-Index-7**

The seven-item version of the Whiteley Index, an established hypochondriasis scale first described by Pilowsky, was developed and validated by Christensen et al. (2003) specifically to assess treatment effects. (t 0, t 1, t 2)

- **TAS**

The „Toronto Alexithymia Scale“ (Bagby et al. 1994) is a 20-item self-report measure of alexithymia with good internal consistency and test-retest reliability and a factor structure congruent with the alexithymia construct (t0). Alexithymia is conceptually related to expected effects of the treatment intervention and will be therefore assessed as a predictor variable.

- **ECR**

The Questionnaire „Experiences in Close Relationships“ (ECR, Brennan et al. 1998, german adaption: the Bochum Adult Attachment Questionnaire, Neumann et al., submitted) measures the two attachment dimensions avoidance and anxiety to characterize the quality of partner attachment (t0).

- **HAQ**

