|              | Anticipating (Planning/ Structuring) the time after the intervention in order to prevent a relapse
regarding: use of gained knowledge                                                                                                                      |
|              | Planning further (psycho or social)therapeutic measures,
Planning further job-related and private activities                                                                                                                                               |
| Means | Written summary of the things that were clarified (letter to the patient, e.g. regarding treatment of symptom / body, relatives, etc)
Written plan of possible changes in daily life
Specifying a concrete goal for the next 3 months on a special form |
| Tip          | Booster session after 3 months, making appointment now!                                                                                                                                                                                                |

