#### **Appointments**

After being screened and interviewed either in a somatic inpatient or outpatient setting and after entering the study, patients in this study arm will have at least three appointments with the physician at the somatic outpatient treatment unit, e.g. a pain center. The respective appointments are six weeks apart at most. Additional appointments are possible, as needed.

- the emphasis of the first appointment is on negotiation of diagnosis and treatment plan
- the emphasis of the second appointment is on interim results and adjustment of treatment measures
- the emphasis of the third appointment is on planning and negotiating the future course of treatment

The amount of time spent during the appointments will vary according to clinical needs.

The patients will be encouraged, but not obliged to withhold treatment with other specialists at the same time.

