## **Physician – patient communication**

Definition of physician-patient communication aims at the following

- to avoid iatrogenic factors in the communication that potentially contribute to the persistence of symptoms and illness beliefs
- to ensure active cooperation of the patient in the treatment process
- to enhance homogeneity of treatment across study sites and physicians
- to enhance patient adherence to treatment

The following components should be included in communicating with the patient:

- information about the diagnoses, including the research diagnosis of multisomatoform disorder
- information about treatment alternatives, including self help strategies and complementary medicine
- enquiry about patient's treatment expectations
- negotiation of treatment decisions ("shared decision")

Principles of patient-centered care, including mutual respect and openness for differing views, should underlie these topics. The practice guideline "Defining the patient-physician relationship for the 21st century" (Johns Hopkins; American Healthways 2004) will be distributed and used as a common reference at all study sites.

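### Depression and suicidality are assessed at 14 scheduled occasions in the therapy arm and 5 in the control arm, so crude SAE counts for this harm are biased against therapy

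*Protocol*

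**What the plan says.** - Section 2.3 (Risks) names one specific harm of the therapy: "there is a risk that during the intervention patients may transiently become more depressive and/ or suicidal". It gives the close watch for this risk to the therapist, through the therapy manual. Section 12 repeats this.
- Section 8.1 extends the usual seriousness criteria: "In PISO, increased depressivity and/ or suicidality is considered as SAE and should be reported in the same way". It gives no instrument, amount, reference time or duration.
- Section 8.2 makes the assessment of these complaints an "integral part of the 12 treatment sessions in the experimental intervention and of the 3 case management sessions in the control condition". It then adds: "All safety parameters will also be recorded at final assessment at 3 months and follow-up at 1 year".
- Section 4.5 makes the therapy sessions weekly over 12 weeks. Sections 4.4 and 6.1 describe three control interviews at monthly intervals. Supplement 3b makes three appointments the minimum, allows more when needed, and sets the spacing: "The respective appointments are six weeks apart at most".
- Supplement 3b introduces the content of the control contacts with "The following components should be included in communicating with the patient". Neither that list nor its sections on appointments and symptom-oriented measures mentions depressivity or suicidality.
- Supplement 3a (Therapy Phase 3) gives the therapy arm a further contact: "Booster session after 3 months, making appointment now".
- Section 4.1 lists the PHQ-D, which "is a brief self-report measure for anxiety, depression and other mental disorders", at t0, t1 and t2. It is a secondary endpoint and is not linked to the safety section.

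**The concern.** An event that is looked for more often is recorded more often. Here the more closely observed arm is the one receiving the treatment under test. The harm is expected to be short-lived and to occur during treatment, so it falls in the 12 weeks when contact frequency differs most. Two patients with the same brief worsening could be counted differently: the therapy patient is seen within a week, while the control patient may recover before the next appointment.

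The counts can have consequences. Section 8.1 makes the coordinating investigator responsible for evaluating trends. Sections 4.6 and 9.4 allow the trial to end on a committee recommendation or a changed balance of risk and benefit. There are no interim analyses, so crude SAE counts are among the few figures available for such a judgement. The undefined word in 8.1 adds a second problem. A worsening that 2.3 expects as part of treatment is also reportable as serious, and sites have no common reference point for deciding when it has occurred.

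**Working it through.** The protocol states no SAE rate and no calculation for safety, so there is no figure of its own to reproduce beyond the contact counts.

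**Scheduled occasions**

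- During treatment (8.2): 12 versus 3, ratio 12/3 = 4.0.
- With the two common assessments (8.2): 12 + 2 = 14 versus 3 + 2 = 5, ratio 14/5 = 2.8.
- With the booster in Supplement 3a, if it serves as a safety occasion (8.2 does not say): 15/5 = 3.0.
- At the common assessments alone: 2 versus 2, ratio 1.0.

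**Visit-overlap model, equal true risk in both arms**

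Assumptions, none of them in the protocol: an episode starts at a uniformly random time in weeks 0 to 12 and lasts D weeks. It is found if a contact falls inside it. Therapy contacts are at weeks 1, 2, …, 12. Control contacts are at weeks 4, 8, 12 (monthly) or 0.5, 6, 12 (close to the six-week maximum). The 3-month assessment is placed at week 12.5. It adds nothing in this model, because any episode it would catch is still present at the week-12 contact.

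An episode is found by the contact at week x if it starts between x − D and x. Detection is the total length of such start times within weeks 0 to 12, divided by 12.

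| D (weeks) | Therapy | Control, monthly | Control, six-weekly |
|---|---|---|---|
| 1 | 12/12 = 100% | 3/12 = 25% | (0.5+1+1)/12 = 21% |
| 2 | 100% | 6/12 = 50% | (0.5+2+2)/12 = 37.5% |
| 4 | 100% | 12/12 = 100% | (0.5+4+4)/12 = 71% |
| 6 | 100% | 100% | 100% |

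If 10% of the 88 patients per arm (section 9.2) had one episode (assumed), that is 8.8 true episodes in each arm. The therapy arm would record about 8.8. The control arm would record:

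- 1-week episodes: 8.8 × 0.25 = 2.2, or 8.8 × 0.208 = 1.8;
- 2-week episodes: 8.8 × 0.50 = 4.4, or 8.8 × 0.375 = 3.3;
- 4-week episodes: 8.8, or 8.8 × 0.708 = 6.2;
- 6-week episodes: 8.8.

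At an assumed 30% share all these counts triple and the ratios stay the same.

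**Cross-check by occasion count**

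Assume instead that each of the 14 or 5 occasions has the same independent chance q of recording an event. The share of patients with a record is 1 − (1 − q)^k, with k = 14 or 5.

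| q (assumed) | Therapy, k = 14 | Control, k = 5 | Ratio |
|---|---|---|---|
| 0.5% | 6.8% | 2.5% | 2.7 |
| 1% | 13.1% | 4.9% | 2.7 |
| 5% | 51.2% | 22.6% | 2.3 |
| 10% | 77.1% | 41.0% | 1.9 |

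Both calculations give the same direction. The first shows that the size depends on episode length.

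**The case against.** The case on the other side is substantial, and part of it stands.

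- **Common visits and extra control visits.** Section 8.2 records all safety parameters in both arms at 3 months and 1 year, and three control appointments is a minimum. This stands, so the fair count is 14 versus 5 and further control visits narrow it. Two late visits still cannot recover a transient worsening during treatment.
- **The overlap model is strict.** It gives no credit for recall at the next visit or for unscheduled contact, and section 8.3 ties the 24-hour report to learning of the event, not to a session. This stands: for a given episode length the control detection rates are low-end figures. Such reports would narrow the gap but would not reverse it.
- **No announced comparison.** The protocol announces no between-arm test of SAEs, and tabulation may be left to an analysis plan that is not at hand. This stands for the table itself. But the assessment schedule and the SAE definition are fixed in the protocol, and no later analysis can recover events that nobody asked about.
- **Silence in Supplement 3b.** It sets out communication, not safety procedures. Supplement 3a is an abbreviated translation that likewise sets out no routine assessment of this harm, and section 2.3 refers to a separate clinical-care manual that is not shown. So the silence does not prove that control monitoring is absent. It shows only that 8.2 claims an assessment which the guideline for those contacts does not mention.

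A reader might infer two stronger points, and the documents support neither. One is that SAE rates cannot be compared between the arms at all. The common recordings and the PHQ-D follow one schedule in both arms, and deaths and hospitalisations depend less on contact frequency. The other is that ordinary questionnaire fluctuation would fill the SAE list. Section 8.1 names no questionnaire, and 8.3 leaves seriousness to the investigator's statement, so no such count can be derived.

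**Conclusion.** The point holds for crude SAE counts of increased depressivity or suicidality. At equal true risk, the schedule in 8.2 biases them against the therapy arm, and the missing reference point in 8.1 leaves the count open to differences between sites. Under the assumed model, detection is about 100% against 21–25% for 1-week episodes, 37.5–50% for 2-week and 71–100% for 4-week episodes, with no difference from 6 weeks. The bias is thus large for brief episodes and absent for long ones. The protocol gives no episode length or rate, but its own description of the risk as transient points to the shorter end. The primary efficacy analysis is not affected. This is a correctable weakness in how one harm is ascertained and is worth changing because the change is cheap.

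**What to change.** In section 8.2, state that the between-arm comparison of this harm uses only data collected on the common schedule:

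- the safety parameters recorded at 3 months and 1 year, including suicidality, which section 4.1 does not say the PHQ-D covers;
- the change in PHQ-D depression score from t0 to t1 and to t2, with the amount that counts as worsening fixed by the sponsor before enrolment.

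Report events found in treatment contacts separately by arm, with the number of contacts held (including any extra control visits and the booster), and do not use them for the arm comparison.

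Reconcile the SAE wording in 8.1 with the transient increase expected in 2.3, including the reference point for an increase. Reconcile 8.2 with Supplement 3b on whether the control contacts include this assessment. Which clinical rule results is for the sponsor to decide.

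The cost is protocol wording and modest extra reporting; the data are already planned in both arms. The downside is that brief episodes between the common visits appear only descriptively, so the comparison is fair but less sensitive to the transient worsening that 2.3 describes.
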